#### Secondary outcomes

Death before discharge.Surfactant treatment within 72 h after randomization.Duration of both NIV and IMV.Duration of oxygen therapy.Bronchopulmonary dysplasia (BPD).Time to achieve full enteral nutrition.Necrotizing enterocolitis.Duration of admission.Cost of admission.Air leak syndrome (including pneumothorax, pneumomediastinum, and pneumopericardium).Nasal trauma, which will be assessed based on a clinical score [40].Comfort score (Neonatal Pain, Agitation and Sedation Scale, N-PASS) [41].

### Participant timeline {13}

Figure 1 The schedule of recruitment, interventions, and assessments (See attachment 1).

**Fig. 1 Fig1:**
[figure not shown]
The schedule of recruitment, interventions, and assessments. t_1:_ immediately after randomisation; t_2:_ 72 h after randomisation; t_3:_ after weaning or failure of allocated treatment; t_4:_ first hospital discharge; RD: respiratory distress; HFNC: high-flow nasal cannula; CPAP: continuous positive airway pressure; NIPPV: nasal intermittent positive pressure ventilation; MV: mechanical ventilation; BPD: bronchopulmonary dysplasia; NEC: necrotizing enterocolitis; N-PASS: Neonatal Pain, Agitation and Sedation Scale

### Sample size {14}

As this study aims to compare the effectiveness and safety of NIPPV, CPAP, and HFNC in infants with GA ≥ 32 weeks, we plan to conduct paired comparisons. Since no studies with identical content to this study have been conducted in the past, we will refer to the following studies for sample size calculation. A trial comparing CPAP and BiPAP including neonates of GA ≥ 34 weeks with transient tachypnea of the newborn, showed that BiPAP had lower treatment failure (CPAP: 20%, BiPAP: 7.9%, P: 0.03) [42]. In addition, a prospective randomised controlled trial comparing CPAP and HFNC in infants with GA ≥ 31 weeks showed higher treatment failure in the HFNC group (HFNC: 20.5%, CPAP: 10.2%, CI: 10.3) [34]. Therefore, we can calculate the sample size of this trial based on the data from the study [34], in which we will use the treatment failure of HFNC and CPAP as primary respiratory support in neonates as a reference. Considering the trial involving multiple comparisons, using an alpha error rate of 0.0167 and a power of 0.8, at least 252 infants should be enrolled in each arm calculated by PASS15.0.5 software, so the total sample size is 756. Considering 5% loss, the sample size would be no less than 795.

### Recruitment {15}

Each participating center’s NICU has established a dedicated position responsible for coordinating the admission and discharge of newborns. We will provide training to the personnel in this position. If a newborn with a gestational age of ≥ 32 weeks is admitted, they will immediately notify the recruitment personnel in charge of this study. All neonates who meet the eligibility criteria can be considered for inclusion in the study and will be recruited by personnel with GCP qualifications. Based on data from participating centers, we estimate that the recruitment period will span approximately 2 years to ensure an adequate sample size for the study.

## Assignment of interventions: allocation

### Sequence generation {16a}

Randomization stratification will be made by GA (< 37 and ≥ 37 weeks’) and by study centers. A 1: 1: 1 allocation ratio and variable block sizes will be used for random allocations within each stratum. Multiple births meeting eligibility criteria will be randomized individually.

### Concealment mechanism {16b}

The allocation of the randomization sequence is conducted through a confidential centralized telephone system, which is concealed from investigators at each of the study centers.

### Implementation {16c}

The randomization sequence is computer generated by dedicated personnel who are not involved in subject inclusion and intervention assignments. All neonates who meet the eligibility criteria can be considered for inclusion in the study and will be recruited by doctors involved in this trial. When an infant meets the eligibility criteria and guardian’s written consent has been obtained, the corresponding assignment based on the randomization sequence will be immediately applied to the infant by respiratory therapists involved in this trial (Fig. 2).

**Fig. 2 Fig2:**
[figure not shown]
Flow diagram of the study

## Assignment of interventions: blinding

### Who will be blinded {17a}

In this trial, blinding of the healthcare professionals involved in delivering the respiratory support methods (doctors, nurses, and respiratory therapists) is not feasible due to the nature of the intervention; it is meaningless to blind the infants. To minimize risk of bias, we developed objective criteria for the primary outcome. Outcome assessors and data analysts will be blinded to the treatment allocation and not involved in the treatment process.

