#### Ventilatory management

In the HFNC group, the initial gas flow setting will be 6 L/min for all infants. The fraction of inspired oxygen (FiO_2_) will be adjusted to maintain pulse oximetry oxygen saturation (SpO_2_) between 90–94%, and the maximum FiO_2_ will be increased up to 0.40 to ensure adequate oxygenation. According to the SpO_2_ and arterial partial pressure of carbon dioxide (PaCO_2_) levels, the gas flow can be increased up to a maximum of 8 L/min.

In the CPAP group, the initial CPAP setting will be 6 cmH_2_O for all infants. FiO_2_ will be adjusted to maintain SpO_2_ between 90–94%. If necessary, the maximum FiO_2_ will be increased up to 0.40 to ensure adequate oxygenation. According to the SpO_2_ and PaCO_2_ levels, the CPAP can be increased up to a maximum of 8 cmH_2_O to optimize respiratory support and maintain appropriate oxygenation and ventilation.

In the NIPPV group, the starting parameters of ventilator will be set as follows:❿ Positive end-expiratory pressure of 6 cmH_2_O (can be increased up to 8 cmH_2_O, according to the SpO_2_ levels);❿ Peak inspiratory pressure (PIP) of 10–15 cmH_2_O (can be increased up to 25 cmH_2_O, according to the SpO_2_ and PaCO_2_ levels);❿ Inspiratory time (IT) of 0.5 s (can be adjusted ranging from 0.4–0.6 s), and rate will be 30 breaths per minute (bpm) (can be increased up to 60 bpm, according to PaCO_2_ levels);❿ FiO_2_ will be adjusted to maintain SpO_2_ between 90–94%, and the maximum FiO_2_ is 0.40.

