### Outcomes {12}

#### Primary outcome

The primary outcome is treatment failure within 72 h after randomization [34]. Treatment failure is defined as meeting one or more of the following criteria when the neonate has received maximal therapy for the assigned treatment:Sustained increase in oxygen requirement: FiO_2_ > 0.40 to maintain SpO_2_ of 90%-94% for more than one hour.Respiratory acidosis: potential of Hydrogen (pH) ≤ 7.20 and PaCO_2_ > 60 mm Hg.Frequent or severe apnea despite drug therapy or respiratory support: two or more apnea events requiring bag-mask ventilation within 24 h, or three or more apnea events requiring intervention (stimulation, increasing oxygen or ventilation pressure) within one hour.Emergency situations such as pulmonary hemorrhage, pneumothorax, heart failure, shock, etc., require endotracheal intubation, or it may be deemed necessary by the pediatrician.

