### Data management {19}

An electronic medical record form will be generated for each enrolled infant to facilitate data collection and management. Respiratory therapists and doctors involved will fill out bedside record forms, which includes ventilatory parameters, blood gas values (PaO_2_, PaCO_2_, pH), and SpO_2_. Data obtained from the bedside record forms and the hospital medical record system (HIS system) will be entered into the electronic medical record form by the data managers. These personnel will receive relevant training to ensure the accuracy, completeness, and confidentiality of the data. The electronic medical record form will be archived in real-time on the online system, with access restricted to authorized personnel only. The principal investigator will periodically review the data, identify missing or erroneous data, and urge local researchers to complete the necessary information (Fig. 2).

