## Discussion

Innovation of this study: Currently, evidence for the use of NIPPV in neonates with GA ≥ 32 weeks is still insufficient. This study will supplement the data on the application of NIPPV in neonates with GA ≥ 32 weeks and compare the effectiveness and safety of the three most used modes in the NICU: CPAP, NIPPV, and HFNC. This will provide more evidence for clinical application of NIV in this population.

Limitations of this study: 1) Blinding of the healthcare professionals involved in the diagnosis and treatment of the neonates is not feasible due to the nature of the ventilation mode being used in the study. However, to minimize potential bias, objective primary outcome criteria have been established. These criteria will be used to assess the outcomes in a standardized and unbiased manner, reducing the impact of lack of blinding on the study results. 2) In this trial, the term “NIPPV” includes both traditional NIPPV and BiPAP. BiPAP is commonly categorized as a form of NIPPV [35]. Previous studies have indicated that both traditional NIPPV and BiPAP show comparable efficacy in preventing treatment failure and the need for MV [51]. Therefore, traditional NIPPV and BiPAP can be considered interchangeable in terms of their effectiveness. Considering that the maximum pressure of BiPAP is lower, traditional NIPPV can be used when the required pressure exceeds the upper limit of BiPAP.

Our study aims to generate robust clinical evidence regarding the efficacy and safety of noninvasive respiratory support in neonates with GA ≥ 32 weeks, and strive to minimize tracheal intubation and mechanical ventilation, and reduce complications related to NIV.

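### Assessor blinding is claimed for the whole trial, but the primary outcome definition depends on arm-specific settings and on an unblinded pediatrician's decision, and N-PASS during ventilation is not shown to be scored blind

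*Protocol article*

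**What the plan says.** The Abstract (Methods) and Trial design {8} describe the trial as assessor-blinded. Who will be blinded {17a} concedes that doctors, nurses and respiratory therapists cannot be blinded, then states: "Outcome assessors and data analysts will be blinded to the treatment allocation and not involved in the treatment process". It names one further safeguard: "To minimize risk of bias, we developed objective criteria for the primary outcome". Procedure for unblinding {17b} calls the design open label, with only assessors and analysts blinded.

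Under Primary outcome, failure within 72 h means meeting at least one of four criteria "when the neonate has received maximal therapy for the assigned treatment". The criteria cover oxygen requirement, respiratory acidosis, apnea, and emergencies that need intubation. The last one ends with "or it may be deemed necessary by the pediatrician".

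Ventilatory management sets the maxima arm by arm. For HFNC, "the gas flow can be increased up to a maximum of 8 L/min". For CPAP the ceiling is 8 cmH2O. For NIPPV there are ceilings on PIP (25 cmH2O), PEEP (8 cmH2O) and rate (60 per minute).

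On the source data, Data management {19} says: "Respiratory therapists and doctors involved will fill out bedside record forms, which includes ventilatory parameters". Data managers then enter these into the electronic form. Plans for assessment {18a} applies N-PASS to infants who are on noninvasive ventilation. Interface gives HFNC infants a smaller cannula, and gives CPAP and NIPPV infants the same choice of prongs or masks.

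**The concern.** A blinded assessor has to be able to apply the outcome definition without learning the arm. Here the definition refers to the assigned mode, and the settings that show whether its maximum was reached also identify the mode. One way of failing is a decision taken by someone who knows the allocation.

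Two things are at stake. First, the trial would be reported and appraised as assessor-blinded on an outcome for which the article does not show this to be so. Second, Objectives {7} states the expectation that NIPPV is better than CPAP and HFNC. Unblinded staff therefore hold a directional expectation when they judge whether support is maximal or intubation is needed. A small arm-dependent difference in those judgements would appear as a treatment effect.

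**Working it through.** **Step 1. Which parts of the assessment can be blind as written**

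| Element | What the article states | Compatible with blinding? |
|---|---|---|
| FiO2, pH/PaCO2 and apnea thresholds | Same in all arms | Yes, taken alone |
| Maximal-therapy condition on failure | Flow for HFNC; pressure for CPAP; PIP, PEEP and rate for NIPPV | Not from raw settings; no masking step described |
| Intubation on the pediatrician's judgement | Decided by treating staff | No; the decision itself is unblinded |
| Stopping the assigned mode at failure ({11b}) | Acted on during care | No; failure is recognised at the bedside before any later review |
| N-PASS | Scored during noninvasive ventilation; scorer not named | Not shown; the interface separates HFNC from the other two arms, but not CPAP from NIPPV |
| Nasal trauma | Clinical score; scorer and timing not in the text | Cannot be determined |
| Data analysis | Analysts blinded | Yes; nothing contradicts it |

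The common thresholds do not settle the matter, because the maximal-therapy condition sits in front of them.

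**Step 2. The plan's own sample size, used as the base for the illustration**

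Inputs from Sample size {14} and Statistical methods {20a}: 20.5% against 10.2%, alpha 0.0167 two-sided, power 0.80. The unpooled formula is

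n = (z₁₋α/₂ + z₁₋β)² × [p₁(1−p₁) + p₂(1−p₂)] / (p₁−p₂)²

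= (2.393 + 0.842)² × (0.205×0.795 + 0.102×0.898) / 0.103² = 251.1.

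Rounded up, this is 252 per arm, as stated. Nothing in this point changes that figure.

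**Step 3. Illustration of what differential judgement could do**

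Assumptions, none of them from the documents: no true difference between two arms, and *d* extra percentage points of failure recorded in one arm only. With n = 252, q = the mean of the two recorded rates and critical value 2.393, the rejection probability is approximately

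Φ[(d − 2.393·SE₀)/SE₁] + Φ[(−d − 2.393·SE₀)/SE₁],

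with SE₀ = √[2q(1−q)/n] and SE₁ = √{[p₁(1−p₁) + p₂(1−p₂)]/n}.

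For a base rate of 15.35% (the midpoint of 20.5% and 10.2%) and d = 3 points: SE₀ = 0.03335 and SE₁ = 0.03332. The result is Φ(−1.495) + Φ(−3.296) ≈ 6.8%. Exact enumeration of the pooled chi-square test gives 6.7%. Exact results for one comparison:

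| Extra failures in one arm | Base 10.2% | Base 15.35% | Base 20.5% |
|---|---|---|---|
| 0 | 1.6% | 1.6% | 1.6% |
| 2 points (about 5 infants of 252) | 4.5% | 3.8% | 3.4% |
| 3 points (about 8 infants) | 8.7% | 6.7% | 5.7% |
| 5 points (about 13 infants) | 23.7% | 17.4% | 14.4% |

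The table shows sensitivity only. It does not estimate a bias, and it does not separate bias at the bedside from bias in later assessment.

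**The case against.** The best defence has several parts.

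- **Masked adjudication is possible.** The numerical thresholds are common to all arms, and a reviewer could work from a record with the mode removed. This stands. A reader might infer that the primary outcome can never be judged without knowing the arm, and the documents do not support that. What they show is a definition that refers to the arm and no described way of masking it.
- **The article is condensed, and extract contents or adjudication steps may sit in the full protocol.** This is fair for procedural detail. It does not remove the conflict between two things the article does state: who is blinded, and what counts as failure.
- **Unblinded staff recording source data does not contradict a separate blinded assessor.** This is correct. The article does not say that assessors see the bedside forms.
- **Some protection remains.** Analyst blinding is uncontradicted, objective thresholds exist, and the article admits that clinicians are unblinded. It would be wrong to conclude that there is no protection against bias.
- **The Discussion does not lean on assessor blinding.** Its phrase "reducing the impact of lack of blinding on the study results" refers to the objective criteria, in a paragraph that lists the absence of clinician blinding as a limitation. A reader might take it as an appeal to blinded assessment, but it is not one. The pediatrician-judgement clause does weaken that appeal to objectivity.
- **Nasal trauma might be scored with no interface in place.** The schedule figure is not shown, and its caption includes a time point after weaning or failure. It cannot be said that this score is taken with the interface in view.
- **The false-positive figures rest on assumed differentials.** This is correct, and they carry no weight beyond illustration.

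**Conclusion.** The point holds in a limited form. Assessor blinding is asserted in four places and conflicts with the primary outcome definition in two respects: the arm-specific maximal-therapy condition and the unblinded pediatrician's decision to intubate. It is also not shown to be achievable for N-PASS during ventilation, at least for HFNC against the other two arms. Nasal trauma is undetermined.

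No sample size or test changes. The consequence lies in how far the primary result can be described as blindly assessed. The size of any bias is unknown. Under assumed differentials of 2 to 5 points, the exact false-positive rate of a single comparison would be 3.4% to 23.7% across base rates of 10.2% to 20.5%, against a nominal 1.67%. The correction is worth making because it is cheap and affects what may be concluded.

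**What to change.** 1. **Reconcile Primary outcome with {17a} and {17b}.** Have the existing data managers give the assessor an extract without mode or settings. It would hold FiO2, SpO2, pH, PaCO2, apnea counts, intubation time, and a yes/no flag for being at the arm's protocol maximum. A mechanical rule applied to the recorded settings should set the flag, so that judgement does not simply move to the data managers. NIPPV has several ceilings, so the rule must say which of them define the maximum; that choice is the investigators'. If this is not done, describe primary outcome assessment as open-label.
2. **Limit the claim in the Abstract, {8}, {17a} and {17b}.** State that bedside failure decisions, the pediatrician-judgement criterion and N-PASS are unblinded. State who scores nasal trauma and when. Claim blinding only where it holds, which includes data analysis.
3. **Pre-specify one sensitivity analysis** of the primary outcome in which failures met only through the pediatrician-judgement criterion are not counted. Masking the assessor cannot remove bias that arises at the bedside, so this is needed in addition to item 1.

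The cost is revised wording, an extract from data already entered and one extra analysis, with no additional staff. The downside is a less favourable description of the blinding.

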### Procedure for unblinding if needed {17b}

The design is open label with only outcome assessors and data analysts being blinded so unblinding will not occur.

## Data collection and management

### Plans for assessment and collection of outcomes {18a}

Prior to the commencement of the trial, the principal investigators will provide training to the data assessors to ensure their thorough understanding of the study protocol and the data to be collected. Clinical information will be collected at the following time points:Before randomization:Information on eligibility; baseline characteristics of study centers, infants, and mothers; diagnosis of respiratory system diseases.After randomization and before intervention:Assessment of the severity of RD using SAS.Following intervention:Ventilatory parameters, blood gas values: PaO_2_, PaCO_2_, pH; SpO_2_.Follow-up:Treatment failure within 72 h after randomization, surfactant treatment within 72 h after randomization, duration of both NIV and IMV, duration of oxygen therapy, BPD, time to reaching full enteral nutrition, necrotizing enterocolitis, cost of admission, duration of admission, and air leak syndrome (including pneumothorax, pneumomediastinum, and pneumopericardium), nasal trauma, comfort score.

The clinical scores involved in this study include the SAS [31], assessment of Nasal trauma based on a clinical score [40], and the Comfort score (N-PASS) [41]. The SAS can be used to assess the severity of respiratory distress in newborns and is an internationally recognized scoring tool [31, 33, 43]. To assess the severity of nasal trauma, we utilized a clinical scoring system developed by Fischer et al. [40]. This scoring system has been employed in several clinical studies for evaluating nasal trauma [44–46]. The score categorizes and rates nasal trauma in newborns and please refer to the reference for a detailed description [40]. In this study, we employed the N-PASS to assess the comfort of newborns undergoing non-invasive ventilation [41]. Multiple system reviews have demonstrated that N-PASS exhibits good measurement performance when used for acute and prolonged pain assessment in both full-term and preterm infants, as well as in specific clinical scenarios such as postoperative and mechanical ventilation situations [47–50].

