**Methods:**

This trial is designed as an assessor-blinded, three-arm, multi-center, parallel, randomized controlled trial, conducted in neonates ≥ 32 weeks’ GA requiring primary NIV in the first 24 h of life. The neonates will be randomly assigned to one of three groups: HFNC, CPAP or NIPPV group. The effectiveness, safety and comfort of NIV will be evaluated. The primary outcome is the occurrence of treatment failure within 72 h after enrollment. Secondary outcomes include death before discharge, surfactant treatment within 72 h after randomization, duration of both noninvasive and invasive mechanical ventilation, duration of oxygen therapy, bronchopulmonary dysplasia, time to achieve full enteral nutrition, necrotizing enterocolitis, duration of admission, cost of admission, air leak syndrome, nasal trauma, and comfort score.

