### Eligibility criteria {10}

#### Inclusion criteria

The inclusion criteria for infants participating in the trial are as follows:They are born at ≥ 32 weeks GA; andTheir birth weight ≥ 1200 g, andRD occurred within 24 h after birth (RD is defined as the presence of any two or more of the following symptoms: tachypnea, chest retraction, or grunting) [33].

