### Intervention description {11a}

Infants enrolled in the study will be randomly assigned to one of the three groups: the HFNC group, CPAP group, or NIPPV group. Once assigned to a specific group, the infants will immediately begin the corresponding intervention based on the assigned group.

Before applying the assigned intervention, each newborn will be assessed the severity of RD using the Silverman Andersen score (SAS) [31]. This approach ensures a standardized and systematic evaluation of RD severity before commencing the assigned intervention, allowing for a consistent baseline comparison across the different treatment groups. Then, the assigned NIV can be applied.

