### Methods for additional analyses (e.g., subgroup analyses) {20b}

Subgroup analyses of the primary outcomes will be performed based on SAS (4–6 points, 7–10 points) [43] and GA (32W ≤ GA < 34W, 34W ≤ GA < 37W, GA ≥ 37W).

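### The severity score behind the planned subgroup is taken after randomisation with no stated masking of the scorer, and its bands leave out eligible infants scoring 3 or less

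*Protocol article*

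**What the plan says.** **Timing.** Plans for assessment and collection of outcomes {18a} separates what is collected before randomisation, "Information on eligibility; baseline characteristics of study centers, infants, and mothers; diagnosis of respiratory system diseases", from a second step: "After randomization and before intervention:Assessment of the severity of RD using SAS". Intervention description {11a} gives the same order, with the arm assigned first and then: "Before applying the assigned intervention, each newborn will be assessed the severity of RD using the Silverman Andersen score". It describes the purpose of the score as "allowing for a consistent baseline comparison across the different treatment groups".

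**Blinding.** Who will be blinded {17a} says that doctors, nurses and respiratory therapists cannot be blinded. Procedure for unblinding {17b} calls the design open label, with only outcome assessors and data analysts blinded.

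**Use of the score.** Methods for additional analyses {20b} states: "Subgroup analyses of the primary outcomes will be performed based on SAS (4–6 points, 7–10 points", and adds three gestational-age bands. Background and rationale {6a} says that the severity subgroup is meant to show how the three modes perform across differing degrees of respiratory distress (RD).

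**Eligibility.** Under Inclusion criteria, "RD is defined as the presence of any two or more of the following symptoms: tachypnea, chest retraction, or grunting". Neither the inclusion nor the exclusion list mentions an SAS value. The abstract describes the population as "requiring primary NIV in the first 24 h of life"; the inclusion list does not repeat that requirement.

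**The concern.** A subgroup variable should be fixed before anyone can know the arm. Randomisation then protects the comparison within each band. Here a clinical rating is made between allocation and the start of support, in a trial whose bedside staff know the allocation, yet the score is used as if it were baseline. If that knowledge shifts the rating differently by arm, the infants in a given band are no longer comparable between arms.

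The bands raise a second problem. Eligibility counts signs without grading them, so nothing in the text prevents enrolment of an infant with a low score. Such an infant belongs to neither band, and the analysis then says nothing about mild RD although it is meant to span the range of severity.

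What is at stake is the credibility and coverage of the trial's one planned severity analysis.

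**Working it through.** **1. Is the timing a slip?** No. {18a} and {11a} independently give the same order: assign, score, then apply the support.

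**2. Is the scorer shielded from the allocation?**
- {17a} and {17b} limit blinding to outcome assessors and data analysts.
- The SAS is not among the primary or secondary outcomes in Outcomes {12}, so blinding of outcome assessors does not clearly extend to it.
- Implementation {16c} has respiratory therapists apply the assignment at once.
- Concealment mechanism {16b} protects the sequence up to the allocation call. It does not protect a rating made after the call.
- {18a} speaks of trained data assessors but does not say who scores the SAS. Data management {19} lists what therapists and doctors write on the bedside form, and the SAS is not in that list.

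The scorer is therefore unnamed. Knowledge of the arm is possible and is not ruled out.

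**3. What could arm-dependent scoring do?** The documents give no SAS distribution, so this is an illustration with assumed inputs and no true effect. Take 180 infants per arm at SAS 4–6 (10% fail) and 70 at 7–10 (30% fail). In one arm only, 18 of the milder infants are scored 7–10.
- If those 18 fail at 10%, the upper band in that arm shows (70 × 0.30 + 18 × 0.10) / 88 = 22.8 / 88 = 25.9%, against 30.0% elsewhere. That is a spurious 4.1 points. The standard error is √(0.259 × 0.741 / 88 + 0.30 × 0.70 / 70) = 7.2 points, so the bias is about 0.57 standard errors.
- If the 18 are borderline infants who fail at 30%, the upper band is unchanged. The lower band becomes (180 × 0.10 − 18 × 0.30) / 162 = 12.6 / 162 = 7.8%, against 10.0%, a spurious 2.2 points.

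Either way the shift is modest beside sampling error, but it is systematic and more recruitment does not remove it.

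**4. Do the bands cover the eligible scores?**

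| Element | SAS limit stated |
|---|---|
| Inclusion criteria | none |
| Exclusion criteria | none |
| Weaning from study interventions | values below and above 3 are used as thresholds |
| Subgroup bands {20b} | 4–6 and 7–10 |

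The protocol itself works with scores of 3 or less, and {20b} has no band for them.

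**5. How many infants?** Sample size {14} gives 252 per arm, 3 × 252 = 756, and no fewer than 795 after 5% loss. The 252 reproduces with the unpooled two-proportion formula (20.5% v 10.2%, two-sided alpha 0.0167, power 0.80), which gives 251.1. The 795 reproduces as 3 × 265, since 252 × 1.05 = 264.6. The share scoring 0–3 is not given. Across an assumed range:

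| Assumed share at SAS 0–3 | Of 795 | Of 756 |
|---|---|---|
| 10% | 80 | 76 |
| 20% | 159 | 151 |
| 30% | 239 | 227 |
| 40% | 318 | 302 |

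This table is separate from step 3, which places every infant at 4–10. The two should not be combined.

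**The case against.** The strongest reply is that little is proven. No section says that an unblinded person scores the SAS. It may be one of the trained assessors in {18a}, and {17a} keeps outcome assessors blinded and out of treatment. That stands: allocation-aware scoring is an inference. It does not dispose of the point, because the text neither assigns the score to a masked person nor places it before the call.

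Second, the score precedes support, so treatment cannot change it, and bias arises only if misclassification differs by arm. That also stands. The illustration rests on invented inputs, and its result lies within sampling noise.

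Third, low scorers may be rare. The abstract's need for primary noninvasive ventilation suggests sicker infants, and the weaning rules treat a score below 3 as one condition for stopping support. This is a fair argument that the upper end of the assumed range is unlikely, but the inclusion list carries no such floor, so the number stays unknown.

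Fourth, severity is not central to the design. It is absent from Objectives {7}, is not a stratification factor in Sequence generation {16a}, and plays no part in the sample size. A reader might take {6a} to make severity a reason for the trial. It gives severity only as the reason for a subgroup analysis.

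**Conclusion.** The point holds in two limited parts.

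1. The score that defines the severity subgroup is recorded after randomisation in an open-label trial, with no stated masking of the scorer. The severity comparison is exposed to a risk of allocation-aware banding. The size of any bias cannot be derived from the documents.
2. The bands omit SAS 0–3 although eligibility sets no minimum. The number of infants affected cannot be determined; 80 to 318 of 795 is only what assumed shares of 10% to 40% would give, not an estimate.

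Three stronger readings are tempting and not supported:
- *That staff who know the arm do the scoring, so the randomised comparison within bands is broken.* The scorer is not named, and differential scoring is a possibility only.
- *That low-scoring infants are lost from the trial's results.* They remain in the primary intention-to-treat analysis and in the gestational-age subgroups. They are missing from the severity subgroup alone.
- *That the main result is contaminated through covariate adjustment.* Statistical methods {20a} adjusts for baseline characteristics that differ at p < 0.2, and {11a} speaks of the SAS in baseline terms. But {18a} lists baseline characteristics before randomisation and the SAS separately, so the text does not settle whether the SAS would enter such a model.

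This is a change worth making for one additional analysis. It does not threaten the primary comparison.

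**What to change.** - **Timing.** In {18a}, move the SAS to the items collected before randomisation and require it to be scored before the allocation call. Amend {11a} to match.
- **Infants already enrolled.** Trial status gives a recruitment start of September 1, 2023. Flag every infant whose SAS was recorded after randomisation and repeat the severity subgroup analysis without them as a sensitivity check.
- **Coverage.** In {20b}, cover every eligible score, either by adding a 0–3 band or by testing a treatment-by-SAS interaction. This needs no new data and can be settled at any time before analysis.
- **Eligibility wording.** If an entry floor was intended, reconcile the inclusion list with the abstract's requirement for primary noninvasive ventilation and state the floor.

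The cost is one existing bedside assessment moved forward by minutes, a flag on the case report form, and amended wording in the sections named. The sample size and the primary analysis do not change.
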